#### Combined intervention (environmental plus individual level)

The environmental plus individual intervention combines all activities of the environmental intervention and all activities of the Phone2Health program.

### Evaluation

Table 1 contains the assessment variables for Community Walks.

**Table 1 Tab1:** Measures for the community walks study at baseline, 12-month, and 24-month follow up assessments

**Level**	**Variable**	**Description** *Objective=OB Self-report=SR*		**B**	**12 mo.**	**24 mo.**
	**Socio-Demographics**					
I	Personal characteristics & behaviors	Race/ethnicity, age, education, health literacy, smoking behavior	SR	X		
I	Food insecurity	*Household Food Security Survey Module Questionnaire* [47]	SR	X		
	**Outcome measures**					
I	Physical activity	*ActiGraph GT3X+ accelerometer-based device* (primary outcome) *Neighborhood Physical Activity Questionnaire* [48]: assesses time spent walking in and outside the neighborhood *Sedentary Behavior Questionnaire* [49]: assesses sedentary behaviors such was sitting while eating, reading, watching TV, etc.	OB SR SR	X X X	X X X	X X X
	**Mediators**					
I	Neighborhood Walkability	*Physical Activity Neighborhood Environment Scale* [50]: assesses public housing development related physical activity attributes, including presence of walking trails, interesting things to look at while walking, etc.	SR	X	X	X
I	Support from HLAs	*Modified Provider Support Measure* [51]: assesses four types of perceived social support: emotional/informational, readiness of change, identifying potential barriers, & positive social interaction	SR	X	X	X
I	Self-efficacy	*Self-efficacy physical activity scale* [52]: assesses confidence to participate in physical activity under various situations (*e.g.,* on weekends)	SR	X	X	X
I	Motivation	*Treatment Self-Regulation Questionnaire (TSRQ*) [53]: assesses motivation to do healthy behaviors and the degree of an individual’s motivation for a particular set of behaviors (*e.g.,* physical activity)	SR	X	X	X
I	Stages of change	*Stages of change for physical activity* [54]: assesses readiness to meet recommended guidelines for physical activity, categorized into five stages (pre contemplation, contemplation, preparation, action, maintenance)	SR	X	X	X
	**Moderators**					
E	PHD characteristics	Manager Interviews *Implementation Climate Scale for Evidence Based Practice* [55] Data from development verified through observation	SR SR OB	X X X		
E	Access to Physical Activity Resources	*Microscale Audit for Pedestrian Streetscapes-abbreviated tool *[56]	OB	X		
I	Neighborhood Social Cohesion	*Social Cohesion scale* [57]: assesses support from neighbors regarding perceived trust, willingness to help, degree to which values are shared, and connectedness among neighbors from residents’ perspective; related to physical and mental health factors among diverse populations [58, 59]	SR	X	X	X
I	Family	*Adaptation, Partnership, Growth, Affection, and Resolution (APGAR)* [60]: assesses level of satisfaction with family relationships & ability to confide in one another in times of trouble, communicate and share issues, support each other’s aspirations in life, and the way family expresses affection	SR	X		
I	Sleep	*Sleep Quality scale* [61]: assesses sleep quality and disturbance over a 7-day recall period	SR	X	X	X
I	Financial Strain	*Satisfaction with financial condition* [62] : assesses persons’ ability to meet payments on their monthly bills	SR	X		
I	Depressive Symptoms	*Center for Epidemiologic Studies Depression Scale (CESD) short form* [63]: assesses depressive symptoms	SR	X		
I	Quality of life	*EQ-5D-3L* [64]: assesses quality of life across domains mobility, self-care, pain/discomfort, and anxiety/depression	SR	X	X	X
I	Stress	*Perceived Stress Scale* [65]: 4-item measure	SR	X		
	**Process measures**					
I	Dose/Reach	HLA completed checklists, # completed Phone2Health calls	OB	X	X	X
I	Dose/Reach	Walking Group/Indoor Activity Form	OB	X	X	X

*I* Individual, *E* Environment

#### Environment-level assessments

We will conduct two types of assessments of the built environment at all study public housing developments. First, we will measure access to physical activity resources and walkability at all 12 public housing developments using the Microscale Audit for Pedestrian Streetscapes-abbreviated tool [56]. The second environment-level assessment is an assessment of public housing development characteristics conducted via an interview and survey of managers of the 12 enrolled public housing developments. The purpose of the interview is to identify development structure and processes that could affect the intervention. We will ask about the type of development (single building, apartments, high-rise, townhouses, etc.), the manager’s experiences working on health promotion activities, current or future physical activity initiatives, presence of any resident advocacy organizations, communication avenues with residents, and common walking areas for residents (to optimal map routes). At the end of the interview, we will administer the Implementation Climate Scale survey tool focusing on readiness to adopt evidence-based practice [55]. Using a structured form, adapted from existing tools [66, 67] study staff will also assess multiple characteristics of the development itself, including development size, number of buildings, structure of buildings, and other on-site facilities, such as courtyards and community gathering spaces. Together, this information was used in the creation of the walking routes and will serve as moderating variables (Table 1).

#### Individual-level measures: evaluation cohort

All eligible and consented participants will be sent a link to complete the surveys; if needed, the Research Assistant will administer surveys in person or over the phone. The Research Assistant will conduct the screening and baseline surveys and will also conduct the follow-up surveys at 12 months and 24 months for each enrolled participant. Standard socio-demographic measures will be assessed. All participants will receive a $40 pre-paid debit card at each completed assessment.

#### Primary outcome measurement: physical activity

Our primary outcome is minutes of moderate intensity daily physical activity. Participants will wear an ActiGraph GT3X+ accelerometer-based device on their hip and the device will be initialized to collect raw data at 30 Hz. The participant will be instructed to wear the device during waking hours every day for 7 days, except during water activities. At minimum, the GT3X+ must be worn for 10 waking hours/d on at least 4 days. Initially, the raw GT3X+ data will be used to estimate time spent in MVPA (physical activity at ≥ 3.0 metabolic equivalents units) using publicly available algorithms developed for adults [68]. The use of this algorithm will also allow for the detection of continuous walking and running bouts to help confirm participants engagement. All device data will be cleaned and processed [69] in R. As updated algorithms and machine learning models are developed, we will explore use of updated techniques to maximize the data outcomes.

#### Process measures

Process measures will be evaluated to monitor implementation of the intervention and to document receipt of the intervention. The HLAs will fill out a checklist after each physical activity event or promotion activity of the Phone2Health program. This information will help investigators determine intervention dosage and process. Specific metrics will include: 1) reach: the number of people who completed HLA walks/physical activity sessions or engaged in Phone2Health program; 2) the dose of the intervention: the number of HLA activities delivered and completed Phone2Health calls; and 3) participants’ feedback and perceptions of the intervention activities.

### Analysis plan

We will “deconstruct” the intervention for the measurement of adherence to the intervention protocol and use these adherence indices in secondary analyses. Adherence data will be collected based on 1) what, how much, and when individual elements were delivered in each development, and 2) what was reported as received by both study staff and HLAs and by residents. We will collect these data for all intervention levels and all components and will enter these data by level into regression models for intervention residents to determine the relative effects of different levels of intervention on physical activity behaviors. These variables will also be used to create cohorts for sensitivity analyses or stratified analyses.

Initial descriptive analyses will include an analysis of the baseline characteristics of participants. Data will be stratified with respect to study groups and the randomization assumption checked by comparing demographic characteristics across groups. Unbalanced characteristics will be included in multivariable models to control for any demographic difference between intervention groups.

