##### Structured walking groups

HLAs will organize walking groups and adjust scheduling around work and childcare commitments of participants. Groups will begin meeting twice weekly and will occur more frequently as participation increases. The main recruitment strategies employed for these groups will be from flyers, from tables with posterboard displays, and by word-of-mouth referrals. Flyers will be distributed in a variety of ways including door-to-door, posting in high traffic areas, placing in mailboxes, and distributing at community events. Walk group participants will gather at a meeting place, such as a community room, within their development. Children are welcome to attend the walks with their parent/guardian to promote family participation and because improvised day care is not sustainable in the long run. Well behaved pets are also invited. All walking sessions will begin with light stretching. The groups then proceed with their walks. After each walk, they return to the meeting place for a post-walk stretching session. In case of inclement weather, all public housing developments have access to a large group room where they will lead indoor exercise classes, such as dance classes like Zumba or dances to upbeat popular music like Soca.

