HLAs will facilitate access to the Phone2Health program for residents who live in developments randomized to receive the I and E+I intervention. The HLAs will obtain verbal informed consent from interested residents and set them up to use the telephone program by entering their phone number, preferred call days/times, and preferred language into a study-specific website. During enrollment, participants will indicate specific times and days they would like to be contacted. If a call is missed, the system will call back 15 minutes later. If that call is missed, the system will call on the second preferred day. After 2 weeks of missed calls, the HLA will contact the participant to troubleshoot any issues the participant is having (e.g., missed calls). Once completed, residents could re-enroll in the 12-week program if they wish to.

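### The secondary dose and adherence regressions rest on self-selected uptake, so they cannot determine the relative effects of the environmental and individual interventions

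*Protocol article*

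**What the plan says.** The Analysis plan section says the team will measure adherence and "use these adherence indices in secondary analyses". The data cover what was delivered in each development and "what was reported as received by both study staff and HLAs and by residents". They go, by level, into "regression models for intervention residents to determine the relative effects of different levels of intervention on physical activity behaviors". The section adds: "These variables will also be used to create cohorts for sensitivity analyses or stratified analyses".

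Three other places show how dose arises:

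- Process measures defines "the dose of the intervention: the number of HLA activities delivered and completed Phone2Health calls".
- Structured walking groups: "Groups will begin meeting twice weekly and will occur more frequently as participation increases".
- The section on the automated phone program fixes the offer at one call a week for 12 weeks. Interested residents consent to join, and "Once completed, residents could re-enroll in the 12-week program if they wish to".

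The randomised comparisons are planned separately under Aim 1. Each intervention arm is compared with control, E+I with E and with I, and a multilevel model tests the E by I interaction.

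**The concern.** The analysis set, the exposure and the purpose are all stated, and the first two do not serve the third. Residents who complete more calls or attend more sessions are likely to be those already more inclined to become active. A regression of activity on dose then mixes what dose does with who takes it. The same holds for cohorts defined by adherence, which are formed after randomisation. The covariate adjustment in the Analysis plan addresses demographic imbalance between study groups, not differences in willingness within them.

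The trial could therefore report that more calls or more sessions work, or that one level outperforms the other, on evidence that would look the same if dose had no effect. That answer could also conflict with the randomised one.

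**Working it through.** The protocol gives no power or error rate for these models, so there is no figure to reproduce. The check asks how often they find a dose effect when there is none.

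**Inputs from the protocol.** 3 developments per arm, 12 in all, 9 of them intervention developments; 50 residents per development recruited, 32 in the between-group sample size; significance level 0.05; powered difference 5 minutes; walking groups starting at two a week.

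**Assumed, not in the documents.** The correlation r between willingness to take part and a resident's own activity change; the intracluster correlation (ICC); the outcome SD; the dose distributions.

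**Step 1: false-positive rates with no true effect.** Simulation A: 9 developments of 32, SD 20, ICC 0.02, calls of 0, 5, 12 or 24, 1,500 runs per setting. Simulation B: 12 developments of 50, up to 12 calls, r applied at both resident and development level, random-intercept regression on the 9 intervention developments, 1,000 runs per setting. Paired entries are ICC 0.02 / 0.05.

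| r | A: calls completed | B: calls completed | B: sessions attended | B: sessions delivered |
|---|---|---|---|---|
| 0 | 5.2% | 6.9 / 8.5% | 6.5 / 7.7% | 3.5 / 6.5% |
| 0.1 | 21.3% | 29.5 / 34.0% | 26.1 / 25.7% | 4.7 / 8.2% |
| 0.2 | 59.0% | 79.8 / 84.2% | 74.3 / 68.3% | 9.9 / 10.4% |
| 0.3 | 91.3% | 98.8 / 99.0% | 96.9 / 95.5% | 16.8 / 18.4% |

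**Step 2: which route matters.** With willingness acting only at development level (correlation 0.5, then 0.9), delivered sessions reject in 5.6 / 8.4% and 9.4 / 12.5% of runs. If only the 6 developments with E are regressed, the rates are 10.4 / 14.7% and 28.2 / 46.1%. The rule on walking-group frequency is thus a real but weaker route. Residents' own uptake drives most of the error.

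**Step 3: size in minutes.** In simulation A the mean spurious coefficient per 12 calls is 2.34, 4.76 and 7.18 minutes at r = 0.1, 0.2 and 0.3. Divided by the SD of 20, these are 0.117, 0.238 and 0.359 SD. The protocol's power statement implies a smaller SD. With 96 per group, 90% power and ICC 0.02, the design effect is 1 + 31 × 0.02 = 1.62, and SD = 5 / [(1.960 + 1.282) × √(2 × 1.62 / 96)] = 8.4 (normal approximation). At that SD the values are 0.98, 2.00 and 3.02 minutes.

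**Step 4: randomised comparator.** Under the same null as simulation B, testing the E and I main effects on the 12 development means rejects in 3.3% to 6.0% of runs at every setting. The model with the interaction term was not simulated.

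**Step 5: leaving out controls.** Write the arm means as control μ, E μ + e, I μ + i, and E+I μ + e + i + s, where s is synergy. With arm indicators and no control arm:

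- E coefficient = (E+I) − I = e + s
- I coefficient = (E+I) − E = i + s

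Each equals its component's own effect only if s = 0. Their difference, e − i, is free of s; their sizes and ratio are not. The two indicators also become correlated. Across 9 developments the covariance is 3/9 − (6/9)² = −1/9 and each variance is (6/9)(3/9) = 2/9, so the correlation is −0.5. Across all 12 the covariance is 3/12 − (6/12)² = 0.

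**The case against.** **The models are secondary, and the randomised answer is already planned.** This stands. A reader might infer that the trial's main conclusions are compromised; they are not. The point concerns only what the dose models may claim.

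**The error rates rest on assumptions.** This stands too. A reader might infer that the models would report a false effect as a matter of course. That needs willingness to be associated with activity change apart from the intervention. This is plausible, but the documents do not quantify it, and at zero correlation the rates are close to nominal. The minutes scale directly with the assumed SD.

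**The participation rule and the missing controls are not the cause.** Correct. It is tempting to blame both. The frequency rule covers walking groups only, since the phone offer is fixed. Adding controls at zero dose to an ordinary regression would leave the association between willingness and uptake inside the intervention developments untouched. What leaving out controls costs is shown in step 5.

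**The two doses may be comparable.** Read alone, "the number of HLA activities delivered and completed Phone2Health calls" suggests a development-level dose for E and a personal dose for I. The documents do not support that reading as a defect: Table 1 lists the Walking Group/Indoor Activity Form as an individual-level dose and reach measure, and the Analysis plan includes receipt.

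**Covariates belong in the statistical analysis plan.** Their absence from an article is no fault, and adjustment could reduce the bias. But the article does state a purpose, to determine relative effects, that adjustment for measured covariates cannot guarantee. The phrase on levels could also mean amounts of intervention rather than E and I. On that reading the dose-response claim is confounded instead of the ranking.

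**Conclusion.** The concern holds in a limited form. As stated, the secondary dose models and adherence-defined cohorts can produce a dose effect and a ranking of E against I when dose does nothing, because uptake is chosen by residents. For completed calls, false-positive rates run from about 21% to 99% at assumed correlations of 0.1 to 0.3, with a spurious effect per 12 calls of roughly 1 to 7 minutes over SDs of 8.4 to 20. At zero correlation the rates are 5% to 9%. Without controls, the separate effects of E and I also depend on additivity, which hypothesis 3 expects to fail. The randomised tests under Aim 1 are untouched.

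**What to change.** In the Analysis plan section:

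1. Take the relative effects of E, I and E+I from the randomised factorial model on all 12 developments, with controls kept. A direct E-against-I comparison is not among the listed tests but is a contrast in that model.
2. Describe the dose regressions and adherence-defined cohorts as observational and exploratory, with no causal or ranking conclusion drawn from them.
3. Adjust them for baseline activity, motivation, self-efficacy and stage of change, all listed at baseline in Table 1.
4. Treat an instrumental-variable analysis using randomised arm as optional. If it is done, state that the exclusion assumption is doubtful for E, because trails, signage, maps and advocacy may act on residents who attend no session, and that there are only 12 clusters.

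The cost is wording and a few covariates, with no new participants or visits. The trial gives up a causal claim from the dose models. The change should be made before outcomes are analysed, because choosing between conflicting rankings afterwards would be post hoc.

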### Design of the Community Walks study

The design of this study, called Community Walks, is a prospective, cluster randomized controlled trial with housing developments as the unit of randomization. A total of 12 developments (8 managed by Boston Housing Authority and 4 privately managed) will be recruited to participate. Four arms will be compared: environmental intervention alone (E) (*n=*3 developments), individual intervention alone (I) (*n=*3 developments), environmental plus individual intervention (E+I) (*n=*3 developments) and an assessment only control group (*n=*3 developments). All intervention activities assigned to a particular development are available to all residents of that development.

To evaluate our outcomes, a subset of participants from each development will be recruited to serve in an evaluation cohort. The cohort will be assessed at baseline, at one-year, and at two-year follow-up time points. Primary and secondary outcomes will be assessed at these times. Baseline data collection is anticipated to finish at the end of 2023, and final results are expected in 2025. Community Walks has received approval from the Boston Medical Center/Boston University Medical Campus Institutional Review Board. When research staff learn of an adverse event, they report the event to the PI who then assesses details of the event and relatedness to study procedures and fulfills reporting requirements as necessary.

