### Recruitment – public housing developments and residents

#### Recruiting public housing developments

Developments are eligible for selection as one of our study sites if they have at least 100 units. A statistician conducted the randomization stratified by management company (Boston Housing Authority/Private) using a computer program, such that 3 developments went to the E group, 3 developments went to the I group, 3 developments went to the E+I group, and 3 developments went to the control.

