##### Between group analysis

The between group hypothesis is tested in three separate bivariate analyses comparing each intervention group to the control group in two primary outcomes based on the cluster-randomized design. We examine change in each primary outcome pre-intervention to post-intervention: 1) the number of minutes of moderate or greater intensity physical activity per week (continuous); and 2) meeting the recommended guidelines of >150 minutes of moderate or greater intensity physical activity per week (dichotomous at individual level, proportion at group level). In addition, we will examine this hypothesis controlling for potential confounding factors and any variables that violate the randomization assumption using multilevel multivariable linear (continuous outcomes) and logistic (binary outcomes) regression models.

Hypothesis 2: Participants living in developments receiving the combined intervention (E+I) will demonstrate even greater increases in the number of minutes of moderate intensity physical activity per week (individual level) and the proportion meeting the recommended physical activity guidelines (development level) from baseline to 24-month follow-up, compared to either intervention delivered singly.

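### Covariates for the adjusted Hypothesis 1 models are chosen from observed imbalance, and neither baseline activity nor the randomisation stratum is fixed in advance

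*Protocol article*

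**What the plan says.** All places are in the Protocol article.

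- **Recruiting public housing developments:** "A statistician conducted the randomization stratified by management company (Boston Housing Authority/Private) using a computer program", with three developments going to each of the four arms. **Design of the Community Walks study** gives the strata sizes: "A total of 12 developments (8 managed by Boston Housing Authority and 4 privately managed) will be recruited to participate".
- **Between group analysis:** Hypothesis 1 is tested in "three separate bivariate analyses comparing each intervention group to the control group". The form of the outcome is given as "We examine change in each primary outcome pre-intervention to post-intervention". A second, adjusted analysis follows: "In addition, we will examine this hypothesis controlling for potential confounding factors and any variables that violate the randomization assumption", using multilevel linear and logistic regression.
- **Analysis plan**, opening paragraphs: groups are compared at baseline, with "the randomization assumption checked by comparing demographic characteristics across groups", and then "Unbalanced characteristics will be included in multivariable models to control for any demographic difference between intervention groups".
- **Table 1** lists the accelerometer measure at baseline, 12 and 24 months under outcome measures, not under socio-demographics.
- **Sample size**, between-group part: the stated power is for the multivariable analysis, so the adjusted model is not peripheral.

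No section names baseline activity or management company as a covariate.

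**The concern.** The plan states a rule for choosing covariates, and the rule works on the wrong information. After a proper randomisation any imbalance is due to chance. A baseline comparison therefore says which variables happened to differ, not which ones predict the outcome. The model is then settled only after the data are seen, and a different chance imbalance would have given a different adjusted estimate.

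The screen also passes over the two variables with the best claim to be in the model. Baseline activity is the outcome measured earlier and is likely to be its strongest predictor. Management company was used to restrict the randomisation. With three developments per arm, precision is scarce, and data already being collected should be used in a way fixed in advance.

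**Working it through.** **1. The plan's own figure.** The between-group section claims more than 90% power for 5 minutes with 96 per group (3 × 32) at 0.05. It gives no SD and no intracluster correlation (ICC), so the figure can be neither reproduced nor refuted. With SE = SD × √[2(1 + 31 × ICC)/96], 90% power needs an SD of at most:

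| ICC (assumed) | Normal | t, 4 df |
|---|---|---|
| 0 | 10.7 | 7.9 |
| 0.02 | 8.4 | 6.2 |
| 0.05 | 6.7 | 4.9 |

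The point here does not rest on this figure.

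**2. What the screen can pick.** Eight authority and four private developments over four arms of three give 2 + 1 per arm if each stratum was split evenly. That split is inferred, because the article gives strata and arm totals only. Under it every arm is one-third private and a balance check shows exactly zero difference. Baseline accelerometer minutes are not a demographic, so they are not screened.

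**3. How often chance triggers the rule.** The article gives no criterion for imbalance. Assume a valid 5% test on each of the six entries under socio-demographics in Table 1 (race/ethnicity, age, education, health literacy, smoking, food insecurity), taken as independent. The chance of at least one flag is then 1 − 0.95⁶ = 0.26 with no real problem present. Correlation between entries would change this figure, and tests that ignore clustering would raise it.

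**4. Baseline adjustment against change.** With correlation r between baseline and 24 months (assumed), variance is 2(1 − r)σ² for change and (1 − r²)σ² with baseline as covariate. The ratio is (1 + r)/2:

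| r | Variance ratio | SE ratio |
|---|---|---|
| 0.4 | 0.70 | 0.837 |
| 0.5 | 0.75 | 0.866 |
| 0.7 | 0.85 | 0.922 |

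This concerns individual-level variance. The gain in the arm contrast also depends on how stable development-level differences are. In a simulation (12 clusters of 40, ICC 0.03, individual r = 0.5, no stratum effect, widths in SD units), the 95% half-width fell from 0.426 to 0.369 with a cluster-level correlation of 0.5. With a cluster-level correlation of 0.9 it fell only from 0.317 to 0.311.

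**5. The stratum term.** It costs one cluster degree of freedom:

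- Four-arm model: 8 to 7 df, critical t 2.306 to 2.365 (+2.6%).
- Pairwise comparison of six developments: 4 to 3 df, critical t 2.776 to 3.182 (+14.6%).

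If the managers differ by d in the analysed outcome, each arm's sum of squares rises by [2(1/3)² + (2/3)²]d² = (2/3)d² on 2 df. The within-arm mean square therefore rises by d²/3. Illustration with assumed SD 10, ICC 0.02 and 32 per development:

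- Cluster-mean variance = 100 × (0.02 + 0.98/32) = 5.06.
- At d = 3 the mean square is 5.06 + 3.0 = 8.06 (+59%). The interval without the stratum is √1.59 × 2.306/2.365 = 1.23 times as wide as with it.
- At d = 0 the interval with the stratum is 2.6% wider.
- Break-even, from 1 + d²/15.2 = (ratio of critical t)²: d is about 0.9 minutes in the four-arm model and about 2.2 minutes pairwise.

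The simulation (individual and cluster correlation 0.5, baseline-adjusted) agrees. Adding the stratum moved the half-width from 0.369 to 0.379 with no manager effect, and from 0.425 to 0.374 with a 0.2 SD effect at follow-up. The SD of the estimated arm difference was the same with and without the term.

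**The case against.** The strongest reply is that this is a journal article without its analysis plan, and that covariate lists, stratum terms and the handling of baseline are commonly left to that plan. That stands for the mere absence of a stratum term. It does not cover the imbalance rule, which the article states outright.

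Several stronger readings are tempting and are not supported:

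- **That the plan can never adjust for baseline or stratum.** This is true of the demographic screen alone. The between-group section also admits possible confounders, which could include either variable. They are unnamed, so nothing is fixed, but nothing is excluded.
- **That the whole Hypothesis 1 result depends on chance imbalance.** The bivariate comparisons carry no covariates. The dependence is confined to the adjusted models, although those are the ones the sample size section says it powers.
- **That the response is definitely follow-up minus baseline.** That is the natural reading of the change wording, but a hypothesis about change can also be tested with a baseline-adjusted or arm-by-time model.
- **That logistic regression cannot fit the guideline outcome.** The article defines that outcome as dichotomous for the individual. A logistic model of guideline status with a time or baseline term is compatible with the text.
- **That omitting the stratum biases the arm difference, or that including it must sharpen it.** With an even split, omission leaves the estimate alone and affects only the error term. No section supports a 3-minute difference between managers. If change is analysed, a stable level difference cancels and the managers would have to differ in change itself.

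**Conclusion.** The concern holds in a limited form. The article chooses covariates for its adjusted models from observed imbalance and unnamed confounders, and it fixes neither of the two covariates that the design supplies. The firm part is the data-dependence of the adjusted estimate, which needs no assumption beyond randomisation.

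The likely gain from baseline adjustment is a 15% to 30% reduction in individual-level variance relative to a change score, for an assumed r of 0.7 down to 0.4. The arm contrast gains less if development-level differences are very stable over time. The case for the stratum term is that the analysis should follow the randomisation. Its effect on precision may go either way and is small on the losing side in a four-arm model. SD, ICC, r, the manager effect and the 2 + 1 split are all assumed or inferred, because the article gives none of them.

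**What to change.** Before the 24-month data are examined, prespecify:

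1. One four-arm multilevel linear model of 24-month minutes on E, I and E × I, with baseline minutes and management company as covariates, a random effect for development and small-sample degrees of freedom. The comparisons with control are then E, I, and E + I + E × I. The same fit gives the Hypothesis 2 contrasts and the Hypothesis 3 interaction.
2. A matching multilevel logistic model of guideline status at 24 months, with baseline minutes as covariate.
3. Any further individual covariates as a short list named in advance.
4. Deletion of the imbalance rule and of the baseline check of the randomisation assumption as a route into the model, or their retention only as a labelled sensitivity analysis. Baseline tables can stay as description.

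The cost is wording and one cluster degree of freedom. No new data are needed. Taking the contrasts from the four-arm model keeps the stratum's price at 2.6% in critical t, against 14.6% in separate six-development comparisons.
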